### TCM syndrome score

2.10

This score form is constitutive of 2 parts: symptoms and signs. There are a total of nine appraisable items including palpitation, shortness of breath, lassitude, asthma, felling cold, chest distress, edema, oliguria, and abdominal distention. Each item consists of 4 levels. The minimum score is 0, and the maximum score is 54. Higher scores indicate more severe conditions. The scores and details of TCM syndromes are presented in Table 2. The scores are determined using the semi-quantitative integral method (0–6 points) according to the severity of clinical symptoms.

**Table 2 T2:** Traditional Chinese medicine syndrome score.

Syndromes	None	Mild	Moderate	Severe
Palpitation	None	Slight palpitations during activities; able to work	Obvious palpitations during activities; relief after rest	Unable to join routine activities
Shortness of breath	No syndrome	Short of breath after slight activity	Short of breath after moderate activity	Short of breath during rest
Fatigued	None	Slight fatigue; able to work	Heavy and barely able to work or complete routine activities	Too heavy to work or complete routine activities
Asthma	None	Slight wheezing; able to work	Frequent wheezing; able to sleep	Unable to lie down and sleep
Felling cold	None	Fear cold	Need to add clothes	Still feel cold after adding clothes
Chest distress	None	Slight	Often	Always
Edema	None	Slight edema morning and night	Pitting edema (+to++)	Pitting edema (>++)
Oliguria	None	Little urine (>1000 mL within 24 h)	Little urine (<400 mL within 24 h)	Little urine (<100 mL within 24 h)
Abdominal distention	None	Slight	Obvious	Like bulge and cannot press

Scores: Mild = 2, Moderate = 4, None = 0, Severe = 6.

Significant effect: Clinical primary and secondary symptoms disappeared partially or completely, syndrome score decreased by > 70%. Effectiveness: Clinical symptoms improved significantly, syndrome scores decreased by 30% to 70%. Null: Treatment syndrome score decreased by < 30%. Aggravation: Post-treatment points exceed pre-treatment points.

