##### NYHA cardiac function classification

2.9.2.3

NYHA cardiac function classification: Cardiac function I, patients with heart disease but unrestricted activity in whom normal physical activity does not cause fatigue, palpitations, shortness of breath, or angina. Cardiac function II, heart function and physical activity are limited by mild heart attack, no discomfort when resting but normal activity can lead to fatigue, heart palpitations, shortness of breath, or angina. Cardiac function III, heart disease, limited physical activity, less than the usual general activity causes symptoms. Cardiac function IV, heart patients cannot perform any physical activity, and in the resting state can experience symptoms of HF or angina pectoris plus aggravating discomfort after physical activity.

Significant effect: Cardiac function was restored to level I or improved by 2 levels.

Effective: Cardiac function improves by 1 but not 2 levels.

No effect: No change in cardiac function; deterioration; cardiac function decreased by 1 or more levels.

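### TCM syndrome score, Table 2: the Mild and Moderate levels for shortness of breath are in the wrong order, and the oliguria row has no level for 400–1000 mL

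*Protocol article*

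**What the plan says.** Section 2.10 of the protocol article describes the score: "There are a total of nine appraisable items", each with four levels, and a total from 0 to 54. The direction is explicit: "Higher scores indicate more severe conditions". The footnote to Table 2 fixes the points: "Scores: Mild = 2, Moderate = 4, None = 0, Severe = 6".

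Two rows of Table 2 are at issue.

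- **Shortness of breath.** Mild is "Short of breath after slight activity", Moderate is "Short of breath after moderate activity", and Severe is breathlessness at rest.
- **Oliguria.** Mild is "Little urine (>1000 mL within 24 h" and Moderate is "Little urine (<400 mL within 24 h". Severe is below 100 mL in 24 hours.

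The same section turns the percentage change in the total into four grades: a significant effect above a 70% fall, effective for 30% to 70%, null below 30%, and aggravation when the total after treatment exceeds the total before it.

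Section 2.9.2.3 gives the NYHA classes. Class II has symptoms on normal activity. Class III is worse and is the state in which "less than the usual general activity causes symptoms". Class IV has symptoms at rest.

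**The concern.** A severity item must rise with severity. A patient who becomes breathless after slight effort is worse off than one who needs moderate effort to become breathless, yet the table gives the first patient fewer points. A rater who applies the table literally records a real improvement as a deterioration. A rater who silently corrects it scores the same patient differently. Either way, the item does not measure what the section says it measures.

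Section 2.4 enrols NYHA II–IV, so the boundary between slight and moderate exertion lies inside the enrolled range. The score is a named secondary outcome, and the abstract says the trial will show whether the formula alleviates symptoms.

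The oliguria row has a different defect. Its mildest abnormal level is attached to a volume above 1000 mL, with no upper limit, and a patient between 400 and 1000 mL fits no printed volume band. What such a patient scores is left to the rater.

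**Working it through.** **Inputs (section 2.10).** Nine items; None 0, Mild 2, Moderate 4, Severe 6; grade cut-offs at 30% and 70%; aggravation if the later total exceeds the earlier one.

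**The plan's own figure.** Maximum = 9 × 6 = 54 and minimum = 9 × 0 = 0. Both agree with the stated range.

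**Order of the breathlessness levels.** From least to most severe, following the NYHA logic of section 2.9.2.3:

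| State | Printed points | Points in severity order |
|---|---|---|
| None | 0 | 0 |
| After moderate activity | 4 | 2 |
| After slight activity | 2 | 4 |
| At rest | 6 | 6 |

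The printed sequence 0, 4, 2, 6 is not monotone. The Severe level follows the expected logic; only the middle two break it. The remaining seven items (setting oliguria aside) run in order of severity.

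**Error in the recorded change, for every possible improvement on this item:**

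| Improvement | Printed change | Change in severity order | Error |
|---|---|---|---|
| Slight → moderate activity | 4 − 2 = +2 | 2 − 4 = −2 | +4 |
| Slight activity → none | 0 − 2 = −2 | 0 − 4 = −4 | +2 |
| Rest → moderate activity | 4 − 6 = −2 | 2 − 6 = −4 | +2 |
| Rest → slight activity | 2 − 6 = −4 | 4 − 6 = −2 | −2 |
| Moderate activity → none | 0 − 4 = −4 | 0 − 2 = −2 | −2 |
| Rest → none | −6 | −6 | 0 |

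Only the first row changes sign. Two moves are understated by 2 points, two are overstated by 2 and one is unaffected. A patient who does not change has no error in the change, although the baseline total can still be off by 2.

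**Effect on the response grades.** Take a patient who moves from slight-activity to moderate-activity breathlessness. The totals for the other eight items are illustrative; the article gives no distribution of them.

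| Other items | Printed total and grade | Total in severity order and grade |
|---|---|---|
| 2 → 2 | 4 → 6, aggravation | 6 → 4, 2/6 = 33.3% fall, effective |
| 8 → 8 | 10 → 12, aggravation | 12 → 10, 2/12 = 16.7% fall, null |
| 20 → 12 | 22 → 16, 6/22 = 27.3% fall, null | 24 → 14, 10/24 = 41.7% fall, effective |
| 10 → 8 | 12 → 12, 0% fall, null | 14 → 10, 4/14 = 28.6% fall, null |

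The first three cases change grade and the last does not. With other items constant, the printed total always rises by 2, so the grade is always aggravation.

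**Size on the whole scale.** One level is 2/54 = 3.7% of the range; the largest error in a change is 4/54 = 7.4%.

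**Oliguria.** The printed bands are above 1000, below 400 and below 100 mL. The interval 400–1000 mL belongs to none of them. Take a rise from 700 to 1500 mL, assuming the 1500 mL patient is still rated as having little urine (2 points), and try three scores for the unassigned band:

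- band scored 0: 0 → 2, improvement recorded as worsening;
- band scored 2: 2 → 2, no change;
- band scored 4: 4 → 2, improvement recorded as such.

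The documents do not say which applies. The 100 mL level lies inside the 400 mL level, which is harmless if the worst level met is scored.

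**The case against.** The best case on the other side is that this is a printing or translation slip. The article contains other slips of wording, and section 2.10 says that scores follow the severity of symptoms, which points the right way. Little urine at more than 1000 mL contradicts itself; with the sign turned round, the bands become below 1000, below 400 and below 100 mL, which are ordered and leave nothing unassigned between 400 and 1000 mL. The case report form is not shown, so raters may have correct wording in front of them. The score is one of several secondary outcomes, and the primary outcome, NT-proBNP, is untouched.

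Most of this stands as a limit on the point, but it does not remove it. The published table is the only scoring rule available, and it contradicts its own stated direction. A plausible cause for the error does not correct it.

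A reader might also infer more than the documents support:

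- **That the treatment effect on this outcome is reversed.** Reversal is shown for individual patients making one particular move. Both arms use the same table, so without a treatment effect the error creates no systematic difference between them, and some moves err in the patient's favour.
- **That many patients are affected.** The article gives no distribution of this item and no baseline totals.
- **That oliguria also scores improvement as worsening.** The 400–1000 mL band has no score; it is not stated to score 0. The reversal appears only under that one assumption.
- **That everyone above 1000 mL gains 2 points.** The item has a None column, and a patient whose urine is not reduced can be placed there.

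**Conclusion.** Wrong as written. The shortness-of-breath row contradicts both the section's rule on direction and the ordering in the article's own NYHA definitions. This needs no assumption beyond reading the table literally. The consequence is a 4-point error in the change for patients who move between the two swapped levels, a 2-point error in either direction for four other kinds of improvement, and misgrading of some individuals around the 30% cut-off or into aggravation. How often this happens cannot be computed from the article. At trial level the supportable claim is added noise in, or attenuation of, one item of nine in a secondary outcome.

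The oliguria row is incoherent as printed: 400–1000 mL cannot be scored. Whether that comes from a misprinted sign or a faulty scale cannot be settled from the article.

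Whether any patient has actually been scored with the printed wording is not known.

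**What to change.** 1. Reorder the shortness-of-breath descriptors in Table 2 so that breathlessness on less exertion scores higher. The points and the 0–54 range do not change.
2. Reconcile the oliguria row with the source scale, for which section 2.10 gives no reference, so that the bands are ordered, leave no gap and are distinguishable from None.
3. Confirm that the case report form carries the corrected wording in both rows.
4. If patients have already been scored, first establish whether raters followed the printed descriptors. Where they did, exchange the 2 and the 4 on the shortness-of-breath item, which recovers the intended score exactly. Where raters had already corrected the order themselves, the exchange would introduce the error and must not be made. Recheck the oliguria item from source notes where these record enough to do so.
5. Complete this before unblinding and document it.

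The cost is one corrected table, one case report form page, and a mechanical recode plus a limited check of source notes if scoring has begun. Sample size, visits and the primary analysis are unaffected.

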### Minnesota Heart Failure Quality of Life Scale

2.11

The Minnesota Heart Failure Quality of Life Scale is widely used to measure the impact of HF on life.^[14]^ This scale involves the impact of HF on patient lifestyle within the last 1 month (Table 3).

**Table 3 T3:** Minnesota heart failure quality of life scale.

Did your heart failure prevent you from living as you wanted during the last month by	No	Very Little				Very Much
1. Causing swelling in your ankles or legs, etc?	0	1	2	3	4	5
2. Making you sit or lie down to rest during the day?	0	1	2	3	4	5
3. Making your walking about or climbing stairs difficult?	0	1	2	3	4	5
4. Making your working around the house or yard difficult?	0	1	2	3	4	5
5. Making your going places away from home difficult?	0	1	2	3	4	5
6. Making your sleeping well at night difficult?	0	1	2	3	4	5
7. Making your relating to or doing things with your friends or family difficult?	0	1	2	3	4	5
8. Making your working to earn a living difficult?	0	1	2	3	4	5
9. Making your recreational pastimes, sports or hobbies difficult?	0	1	2	3	4	5
10. Making your sexual activities difficult?	0	1	2	3	4	5
11. Making you eat less of the foods you like?	0	1	2	3	4	5
12. Making you short of breath?	0	1	2	3	4	5
13. Making you tired, fatigued, or low on energy?	0	1	2	3	4	5
14. Making you stay in a hospital?	0	1	2	3	4	5
15. Costing you money for medical acre?	0	1	2	3	4	5
16. Giving you side effects from treatments?	0	1	2	3	4	5
17. Making you feel you are a burden to your family or friends?	0	1	2	3	4	5
18. Making you feel a loss of self-control in your life?	0	1	2	3	4	5
19. Making you worry?	0	1	2	3	4	5
20. Making it difficult for you to concentrate or remember things?	0	1	2	3	4	5
21. Making you feel depressed?	0	1	2	3	4	5

### Safety assessments

2.12

AE time, severity, duration, action taken, and outcomes will be recorded truthfully on the designated case report forms (CRFs) during the study. Mild, moderate, and severe labels will be used to describe the intensity of each AE and assess possible associations between each AE and the study or control drug. If a severe AE occurs during the trial, the patients will be suspended from the trial and treated as a lost case. For the safety assessment, the patients’ blood, urine, and kidney and liver function will be tested before and after treatment. To protect privacy, all participants will be visited in a closed room and given the option to withdraw at any time.

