**Methods/design::**

This randomized, double-blind, placebo-controlled clinical trial will evaluate the efficacy and safety of SGF in the treatment of DHF. A total of 130 patients with DHF will be enrolled in the trial and treated with SGF granules or placebo for 12 weeks and followed up for 12 weeks. The primary outcome measurement will be to changes in plasma N-terminal brain natriuretic peptide precursor before versus after treatment, while the second primary outcome measurement will be changes in heart function before versus after treatment and the 12-week follow-up period. It will also include echocardiography, a cardiopulmonary exercise test, cardiac function grading, traditional Chinese medicine syndrome score, and the Minnesota Heart Failure Quality of Life Scale. Adverse events will be evaluated throughout the trial.

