#### Primary outcomes

2.9.1

NT-proBNP levels will be determined using an enzyme-linked immunosorbent assay kit before and after drug administration (week 0 and week 12).

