### Sample size

2.13

One study^[15]^ showed that HF patients whose NT-proBNP levels decreased by more than 30% had better clinical prognosis. In this study, it was estimated that the decrease in plasma NT-proBNP in the treatment group after treatment would reach 42%. Formula n^[16]^$n={\left[\frac{\left(u_{\alpha }+u_{\beta }\right)}{\delta /\sigma }\right]}^{2}+\frac{1}{2}u_{\alpha }^{2}$ was calculated according to the sample size, where standard deviation (instead of σ) is set to 30%, α = 0.05, uα = 1.645, β = 0.1, uβ = 1.282, and δ = 42–30 = 12.

The sample size was calculated as 54 cases, considering a withdrawal rate of no more than 20%, the sample size of this study was determined to be 130 people with a ratio of the experimental and control groups of 1:1 for 65 people in each group.

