### Data collection and monitoring

2.14

In this 24-week trial, all participants will be treated with SGF or SGF placebo for 12 weeks and followed up for another 12 weeks. All data will be entered into the designated database that will be exclusively managed by the research team members. Electronic data files, including databases, analysis programs, analysis results, and explanatory files, will be classified and stored in multiple backups on different recording media and properly stored to prevent damage. All of the original files shall be kept in accordance with the unified requirements of scientific research management, and the management data shall be transmitted in time.

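### The severe-AE rule ends follow-up as well as treatment, so week-12 NT-proBNP and later safety data go missing in an outcome-dependent way that can bias the comparison

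*Protocol article*

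**What the plan says.** Section 2.12 (Safety assessments) states the rule: "If a severe AE occurs during the trial, the patients will be suspended from the trial and treated as a lost case". Severity there is a grade of intensity: "Mild, moderate, and severe labels will be used to describe the intensity of each AE". The link between an event and the study or control drug is assessed separately and is not a condition of the rule.

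The same section has the event itself documented: "AE time, severity, duration, action taken, and outcomes will be recorded truthfully on the designated case report forms (CRFs) during the study". It also sets laboratory safety tests at two times; blood, urine, "kidney and liver function will be tested before and after treatment".

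Three other places bear on the rule:

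- Section 2.9.1: the primary outcome, NT-proBNP, is measured "before and after drug administration (week 0 and week 12".
- Section 2.14: "all participants will be treated with SGF or SGF placebo for 12 weeks and followed up for another 12 weeks". No exception is made for severe events.
- Abstract, Methods/design: "Adverse events will be evaluated throughout the trial".

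Section 2.13 allows for losses with the words "considering a withdrawal rate of no more than 20" per cent. It does not say whether patients removed after a severe event fall within that allowance.

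**The concern.** Stopping study drug and stopping observation are two decisions, and section 2.12 makes them one. A patient who has a severe event is still a randomised patient whose week-12 result can usually be obtained. Calling that patient lost creates a missing value where none was unavoidable.

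The missingness is also tied to outcome. Section 2.4 admits NYHA classes II to IV, so a severe event may be the heart failure itself getting worse, and NT-proBNP may well be higher in such a patient. Sections 2.9.2.3 and 2.10 have categories for worsening on the NYHA class and the TCM score, and the rule takes out patients likely to fall into them. The abstract also expects the trial to show an effect on readmission, yet a readmission that comes with a severe event would end that patient's follow-up.

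If the experimental treatment causes severe events, leaving these patients out flatters it. If it prevents them, leaving out more placebo patients hides part of the benefit. Blinding does not prevent either. On safety, observation stops in the patients for whom further observation is most informative.

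**Working it through.** **Inputs from section 2.13.** Planned difference δ = 42 − 30 = 12 percentage points; SD 30; uα = 1.645; uβ = 1.282; 65 patients per group; withdrawal up to 20%. The documents give no severe-AE rate and no NT-proBNP change after such an event, so both are assumed below.

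**The plan's own figure.** [(1.645 + 1.282)/(12/30)]² + ½ × 1.645² = 53.5 + 1.4 = 54.9, against a stated 54. Then 54 × 1.2 = 64.8, rounded up to 65 per group. These reproduce closely, and the present point does not depend on them. The 20% allowance (13 of 65 per group) adds patients. It does not correct a bias.

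**What goes missing, by timing of the event.**

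- Event before week 12: the week-12 NT-proBNP, the week-12 exercise test and other secondary outcomes, the after-treatment laboratory tests (unless taken at exit, which is not stated), and all later adverse events.
- Event in weeks 13 to 24: the week-12 NT-proBNP has already been drawn. The rest of follow-up is lost.

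The rates below are therefore rates before week 12.

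**Bias if removed patients are not in the analysis.** Let pT and pC be the severe-AE rates on SGF and placebo. Let mT and mC be the mean falls in patients without such an event, and let patients with one fall by d points less in either arm.

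- Difference in all randomised patients: (mT − pT·d) − (mC − pC·d)
- Difference in those remaining: mT − mC
- Bias in favour of SGF: (pT − pC) × d

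| Assumed rate, SGF v placebo | d = 30 | d = 60 | Share of 12 |
|---|---|---|---|
| 5% v 5% | 0 | 0 | 0 |
| 10% v 5% | +1.5 | +3.0 | 12.5% to 25% |
| 15% v 5% | +3.0 | +6.0 | 25% to 50% |
| 20% v 5% | +4.5 | +9.0 | 37.5% to 75% |
| 5% v 10% | −1.5 | −3.0 | 12.5% to 25%, against SGF |

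With 65 per arm, 10% against 5% is 6.5 against 3.25 patients. The 15% and 20% rows only show how the formula scales, and the conclusion does not rest on them.

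**Effect on the test at 10% v 5%.** The patients left are 65 × 0.90 = 58.5 and 65 × 0.95 = 61.75. SE = 30 × √(1/58.5 + 1/61.75) = 5.47. A bias of 1.5 to 3.0 is 0.27 to 0.55 SE. By the normal approximation, with no true difference in all randomised patients, a two-sided 5% test then rejects with probability 0.059 to 0.085.

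**When d differs by arm.** Assume equal rates f and the same rise r after the event in both arms, a 42% fall in other SGF patients and a 30% fall in other placebo patients. The last is an assumption, since section 2.13 gives 30 only as the figure subtracted. Bias = f(42 + r) − f(30 + r) = 12f: 0.6 points at f = 5% and 1.2 at f = 10%, which is 5% to 10% of δ.

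**The case against.** Four stronger readings are tempting, and the documents do not support them.

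- **A reader might infer that severe events vanish from the safety results.** They do not. Section 2.12 has each event's time, severity, duration, action and outcome put on the CRF. What is at risk is what follows: later events and the after-treatment tests.
- **A reader might infer that the comparison is certain to be biased.** The rule is the same in both blinded arms. With equal rates and equal d the bias is zero, and otherwise its sign can go either way.
- **A reader might infer that the protocol excludes these patients from the primary analysis.** The term for a lost patient suggests it, but no section says so. Section 2.16 defines no analysis set, and an unseen SAP may do so. This is a fair limit on the point, but no SAP can recover a blood sample that was never taken. It could only impute.
- **A reader might take the error in the SGF arm alone as the size of the problem.** With a 42% fall in other SGF patients, a rate f of 5% to 10% and a rise of 0 to 50 after the event, f × (42 + rise) is 2.1 to 9.2 points, or 18% to 77% of 12. That sets a one-arm error against a between-arm difference. It would hold only with no corresponding error on placebo, for instance no severe events there, which is implausible if such events come partly from the underlying disease.

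It can also be said that suspension might be temporary, or that section 2.14 describes only the general course of the trial. Neither saves the sentence: counting the patient as lost rules out a temporary pause, and no exception is written into section 2.14 or the abstract.

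**Conclusion.** The rule is wrong as written. It ends observation along with participation, it contradicts the follow-up described in section 2.14 and the abstract, and it makes missing data depend on a post-randomisation outcome plausibly related to the primary endpoint. Because the harm arises when data are not collected, it has to be dealt with in the protocol.

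The size cannot be fixed from the documents. Under modest assumptions (5 percentage points' difference in severe-AE rates, d of 30 to 60) the bias is 1.5 to 3.0 points in either direction, an eighth to a quarter of the planned 12. With equal rates it is zero if d is equal, and about a point or less in the unequal-d case worked above. These figures assume that removed patients are left out of the comparison, which the text implies but does not state.

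**What to change.** Replace the sentence in section 2.12 with text to this effect: *Whatever is decided about study drug, a patient with a severe adverse event remains in the trial for the week-12 NT-proBNP, the other outcomes and adverse-event follow-up to week 24, unless consent is withdrawn. The patient is analysed in the assigned arm. Only a patient who cannot be contacted or who withdraws consent counts as lost.*

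Then reconcile section 2.12 with section 2.14 and with the abstract's statement on adverse events. When study drug should be stopped is a clinical matter and is not touched by this change.

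The cost is small. At the assumed 5% to 10%, it means visits and a week-12 blood draw for roughly 3 to 7 patients per arm (65 × 0.05 = 3.25; 65 × 0.10 = 6.5). Some of these values will be off treatment and may slightly dilute the estimated effect.
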